### The interventions

Both interventions will consist of eight sessions with a length of 120 minutes each, which will be held at weekly intervals in an outpatient setting at the University Medical Center of Freiburg and the University Medical Center Hamburg. Each treatment group will consist of eight to twelve participants.

MBCT is based on mindfulness training as developed by Jon Kabat-Zinn at the University Medical Center of Massachusetts, combined with psychoeducational elements from cognitive therapy. A detailed description of the original intervention can be found in Segal, Williams & Teasdale [15]. In the proposed trial, a modified version of the manual will be applied: The mindfulness elements are adopted from the original manual, and the cognitive elements are tailored to patients with OCD [35].

We intend to use an education program as an active control condition in order to control for unspecific effects of a group treatment. The program (OCD-EP) consists of a presentation and education about the etiology, mechanisms and maintaining factors of OC symptoms, metacognitive and neurobiological perspectives on OCD, information on existing pharmacotherapeutic and psychological treatment modalities and relapse prevention, group sharing and discussion. Behavior therapy techniques or mindfulness interventions are not part of the program.

The treatment sessions will be held by experienced behavioral therapists with longstanding experience in MBCT respective psychoeducation of OCD.

### Setting

Overall, eight MBCT- and eight OCD-EP-groups will be conducted (four MBCT- und four OCD-EP-groups at each site). The baseline assessments (T0) and post-assessments (T1) will be performed directly before respectively after the interventions. The first follow-up (T2) will be six months and the second (T3) will be 12 months after the end of the intervention.

The two participating centers will be the University Medical Center Freiburg and the University Medical Center Hamburg-Eppendorf. Both centers will recruit equal proportions of participants. Potential distortions due to the bicentric approach will be controlled by a stratification and by homogeneous study conditions (same room equipment, same training of the therapists, same measures, etc.).

The bicentric study was approved by the ethics commission of Freiburg University Medical Center. In accordance with the Declaration of Helsinki, all participants will be informed in detail about the design and purpose of the study. Each participant will be required to sign a written consent form and will have the freedom to withdraw consent and quit the study at any point in time. Data will be documented anonymously in a case report file (CRF), which will be stored at the University Medical Center Freiburg for 10 years. All necessary personal data will be kept confidential. All sessions will be videotaped, supervised and checked for adherence. Supervision will be provided by [name], University of Esslingen.

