### Sample size

A power analysis was performed with the program “G*Power” [42]. Based on the pilot data, on results of comparable studies [24,43] and on theoretical considerations, we assume a between-group effect size of *d* = 0.5 favoring MBCT. Assuming an a priori test power of 0.8, a total sample size of *n* = 128 (*n* = 64 per intervention) will be sufficient to detect this effect by an *F*-test in an ANOVA at *p* < .05 level of significance for a group × timepoint interaction. We assume a dropout rate of approx. 15% and thus target a total sample size of *n* = 148.

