### Statistical analyses

Between-group comparisons at baseline will be performed using analyses of variance for the continuous variables and Fisher’s exact test for the categorical variables. Means and standard deviations will be calculated for descriptive purposes. The main analyses will be computed using analyses of covariance in view of statistical studies suggesting that controlling for the baseline score is superior to simple pre-post comparisons and usually leads to an increase in power. An advantage of this type of analysis over mixed models is that it accounts for baseline differences and regression to the mean (i.e. higher scores usually yield greater improvement). The rates of patients achieving response and/or remission and the relapse rates in both groups will be compared using Fisher’s exact test. The time to relapse will be estimated using Kaplan-Maier survival analyses. Survival curves will be compared using a log-rank-test. A cox-regression will be performed to analyze variables influencing the time to relapse. In order to prevent distortions, the intent-to-treat principle will be used. Multiple imputation will be adopted to estimate post-treatment and follow-up scores for non-completers (i.e. no data available at reassessment). The multiple imputation principle is considered superior to the last observation carried forward method (LOCF) [64]. When using the LOCF, follow-up data can be difficult to interpret [10].

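### The two centres are handled by stratification, but the main ANCOVA as described names only the baseline score; adding centre as a fixed effect is a small, nearly free gain

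*Protocol article*

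**What the plan says.** Protocol article, Setting: "Potential distortions due to the bicentric approach will be controlled by a stratification and by homogeneous study conditions". The same section fixes the layout. "Both centers will recruit equal proportions of participants", and there are to be "four MBCT- und four OCD-EP-groups at each site". Both arms are therefore run in equal numbers of groups at each centre.

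Protocol article, Statistical analyses: "The main analyses will be computed using analyses of covariance". The reason given is that "controlling for the baseline score is superior to simple pre-post comparisons and usually leads to an increase in power". The baseline score is the only covariate named. Neither centre, site nor a stratification factor appears in that section.

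Protocol article, Sample size: 64 patients per arm, with an assumed effect of d = "0.5 favoring MBCT" and power of 0.8 at the .05 level, from an ANOVA F-test. No centre term is mentioned there either.

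**The concern.** The article does address centre effects, and both controls it lists act in the design: a stratification and similar conditions. The analysis it describes does not pick the factor up.

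When arms are balanced within centre, a centre difference adds equally to both arm means and cancels from their difference. The true sampling error of the treatment estimate therefore contains no centre component. A model without centre still counts that component as residual noise, so its standard error describes a less precise design than the one that was run.

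What is at stake is precision. The confidence interval for the Y-BOCS difference is somewhat wider than it needs to be, and the test rejects a little less often than its nominal level, under the null and under the alternative. The design has almost no spare power, so even a small loss takes it just below its 0.80 target.

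**Working it through.** **Inputs from the protocol article.** 64 per arm, d = 0.5, power 0.8, two-sided 0.05 (Sample size); two centres of equal size with arms balanced within each (Setting); ANCOVA on the baseline score (Statistical analyses).

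**Assumed input.** The centre difference D that remains after baseline adjustment, in residual SD units. The article gives none, so a range is used. Patients are treated as independent.

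**Step 1: reproduce the plan's own figure.** The F-test with f = 0.25 and 1 and 126 degrees of freedom, which is the same as a two-sided t-test with d = 0.5 and 64 per arm, has power 0.8015. The stated total of 128 is reproduced. The normal approximation used in Step 2 gives Φ(0.5 × √32 − 1.96) = Φ(2.828 − 1.960) = Φ(0.868) = 0.807.

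**Step 2: effect of leaving centre out.** With residual SD 1:

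- Variance that two equal centres add to the residual: s = D²/4.
- Inflation of the reported standard error: √(1 + s). The true standard error is unchanged because the arms are balanced within centre.
- Type I error = 2 × [1 − Φ(1.96 × √(1 + s))].
- Power = Φ(0.5 × √32 − 1.96 × √(1 + s)).

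| D (residual SD) | s | √(1 + s) | Type I error | Power |
|---|---|---|---|---|
| 0 (same as centre in the model) | 0 | 1.000 | 0.050 | 0.807 |
| 0.25 | 0.0156 | 1.008 | 0.048 | 0.803 |
| 0.5 | 0.0625 | 1.031 | 0.043 | 0.790 |

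For D = 0.5: 1.96 × 1.031 = 2.020, so type I error is 2 × [1 − Φ(2.020)] = 0.043 and power is Φ(2.828 − 2.020) = Φ(0.808) = 0.790.

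**Step 3: simulation check.** Two centres × two arms × 32 patients, 8,000 runs per setting, an assumed baseline–post correlation of 0.5, and a treatment effect of 0.5 residual SD. Here the centre effect is stated in SDs of the post score; divide by √0.75 = 0.866 to get residual SDs.

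| Centre effect (post-score SD) | In residual SD | Type I error without / with centre | Power without / with centre |
|---|---|---|---|
| 0 | 0 | 0.047 / 0.047 | 0.795 / 0.797 |
| 0.2 | 0.23 | 0.047 / 0.048 | 0.798 / 0.802 |
| 0.3 | 0.35 | 0.044 / 0.047 | 0.786 / 0.794 |
| 0.5 | 0.58 | 0.043 / 0.052 | 0.777 / 0.799 |
| 0.8 | 0.92 | 0.029 / 0.047 | 0.739 / 0.800 |

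Monte Carlo standard error is about 0.0045 for power and 0.0024 for type I error, so the first three rows show little beyond noise. The 0.5 row loses more power than D = 0.5 in Step 2 mainly because it corresponds to 0.58 residual SD. The last row lies outside the main range and only shows the direction. With no centre effect, including centre costs no visible power.

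**The case against.** The strongest objection is that this argues from silence. The statistical section explains why ANCOVA was chosen; it does not give a closed list of covariates. A condensed article may leave design covariates to a fuller plan, and no such plan is at hand. This stands in part: nothing in the article excludes centre, so the point can only concern the model as described. But the article does not simply leave the topic open. It says what controls centre effects and what the main model controls for, and centre is missing from the second.

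Next, the article says only that there is a stratification. It does not say that allocation is stratified by centre, and a stratified analysis is a possible, though less natural, reading. This also stands. Under that reading the proposed sentence would only make explicit what is already meant.

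Third, the quoted sentence is about distortion, and on that it is right: with arms balanced within site, omitting centre does not bias the comparison. A reader might infer from a test that is off its nominal level that the primary test is invalid or that false positives are inflated. The figures do not support that. The error rate is below 0.05, never above it.

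Finally, a centre difference in severity already present at baseline would largely be absorbed by the baseline covariate. Only the remaining difference matters, and its size is unknown.

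**Conclusion.** The point holds as a minor one. The design controls for centre and the main ANCOVA as described does not. Followed as written, the primary comparison stays unbiased but gives up a little precision if the centres differ after baseline adjustment. At an assumed 0.25 to 0.5 residual SD, the reported standard error is 0.8% to 3.1% too large, type I error is about 0.048 to 0.043, and power falls by 0.4 to 1.7 percentage points from 0.807. Below that range the effect is negligible.

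This rests on three assumptions: that the stratification means allocation balanced by centre, that the remaining centre difference lies in the range shown, and that patients are independent. How the therapy groups themselves should be modelled is a separate question, on which this point does not depend.

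**What to change.** Add one sentence to Statistical analyses: centre (two levels) enters as a fixed effect, alongside baseline Y-BOCS, in the primary ANCOVA. Do the same in the follow-up ANCOVAs and in the secondary-scale ANCOVAs (each with its own baseline score), and include centre in the multiple-imputation model so that imputed scores are consistent with the analysis. In Setting, say explicitly that allocation is stratified by centre, if that is what is meant.

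The cost is one degree of freedom and no extra data. The total of 128 need not change. The response, remission and relapse rates are compared by Fisher's exact test, which takes no covariate, and can stay as planned for this purpose. The sentence should be fixed before any unblinded outcome data are analysed.

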### Inclusion and exclusion criteria

The main inclusion criterion of our study is a primary diagnosis of obsessive-compulsive disorder (ICD-10 F42.-). Participants should suffer from clinically relevant OC symptoms, i.e. a Y-BOCS global score >12 or subscore of ≥8 in either obsessions or compulsions at study inclusion. Participants are required to be between 18 and 70 years of age and to give informed consent. Since we aim at testing the efficacy of MBCT for patients who are still symptomatic after treatment, only patients who completed at least 20 sessions of CBT with ERP prior to study inclusion will be eligible.

The criteria are aiming at a preferably wide generalizability of the results. However, patients who require a different treatment due to comorbid conditions or whose condition gives reason to expect an inability to benefit from a group treatment will be excluded from participation. These are patients with current manic episode or manic episode within 5 years before study inclusion (ICD-10 F30.-), patients with severe depressive episodes according to ICD-10 criteria, a history of psychosis (ICD-10 F20-F29), current substance dependence (ICD-10 F1x.2), borderline personality disorder or Asperger syndrome (ICD-10 F84.5). Further exclusion criteria are suicidal tendencies according to the Suicidal Behaviors Questionnaire-Revised (SBQ-R), severe neurological disorders or an intelligence quotient <70 as measured by the Test of Word Power (WST). Moreover, to prevent confounding effects, patients with begun or altered psychotherapeutic treatment or medication within 12 weeks before study inclusion are also excluded. A change of dosage within the same drug, however, is tolerated.

### Sample size

A power analysis was performed with the program “G*Power” [42]. Based on the pilot data, on results of comparable studies [24,43] and on theoretical considerations, we assume a between-group effect size of *d* = 0.5 favoring MBCT. Assuming an a priori test power of 0.8, a total sample size of *n* = 128 (*n* = 64 per intervention) will be sufficient to detect this effect by an *F*-test in an ANOVA at *p* < .05 level of significance for a group × timepoint interaction. We assume a dropout rate of approx. 15% and thus target a total sample size of *n* = 148.

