**Methods/design:**

This study is a prospective, bicentric, assessor-blinded, randomized, actively-controlled clinical trial. 128 patients with primary diagnosis of OCD according to DSM-IV and no or only partial response to CBT will be recruited from in- and outpatient services as well as online forums and the media. Patients will be randomized to either an MBCT intervention group or to a psycho-educative coaching group (OCD-EP) as an active control condition. All participants will undergo eight weekly sessions with a length of 120 minutes each of a structured group program. We hypothesize that MBCT will be superior to OCD-EP in reducing obsessive-compulsive symptoms as measured by the Yale-Brown-Obsessive-Compulsive Scale (Y-BOCS) following the intervention and at 6- and 12-months-follow-up. Secondary outcome measures include depressive symptoms, quality of life, metacognitive beliefs, self-compassion, mindful awareness and approach-avoidance tendencies as measured by an approach avoidance task.

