## Methods/Design

### Study design

The study design is shown in Figure 1. In a prospective, bicentric, assessor-blinded, randomized, actively-controlled clinical trial, 128 patients with OCD according to DSM-IV-criteria will be randomly assigned to one of two groups: the studied intervention consists of 8 two-hour-sessions of MBCT, the control condition consists of 8 two-hour-sessions of OCD-EP. MBCT and OCD-EP will be comparable regarding treatment setting.

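### The abstract and the design section randomise 128 patients, but the sample-size section makes 128 the number needed before dropout and targets 148

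*Protocol article*

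**What the plan says.** Three places in the article give a total number of patients.

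- Abstract, Methods/design: "128 patients with primary diagnosis of OCD according to DSM-IV and no or only partial response to CBT will be recruited".
- Methods/Design, Study design: "128 patients with OCD according to DSM-IV-criteria will be randomly assigned to one of two groups".
- Methods/Design, Sample size: "we assume a between-group effect size of *d* = 0.5 favoring MBCT"; with power set at 0.8 and a significance level of .05, "a total sample size of *n* = 128 (*n* = 64 per intervention) will be sufficient to detect this effect". The section closes with "We assume a dropout rate of approx. 15% and thus target a total sample size of" 148.

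Three other statements bear on the point. The interventions and Setting sections plan 16 treatment groups (eight per arm) of eight to twelve participants. Statistical analyses plans ANCOVA adjusted for baseline as the main analysis. The same section follows intent-to-treat, with multiple imputation for patients who are not reassessed.

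**The concern.** In the Sample size section, 128 is the number before the allowance for dropout and 148 is the target. In the abstract and the Study design section, 128 is the number entering the trial: the verbs there describe recruitment and random assignment, not completion. The two uses cannot both be right, and no sentence says that 128 means patients retained or that 148 replaces it.

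The number to randomise is a core design figure and the benchmark for complete recruitment. If the team worked to the figure in the abstract and design section, the dropout allowance that the plan itself judged necessary would disappear, and power would fall below the stated 80% unless something else made up the loss.

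**Working it through.** **Inputs from the article.** d = 0.5, alpha .05, target power 0.8, N = 128 in two equal arms, dropout about 15% and target 148 (all Sample size); 128 randomised (Abstract, Study design); 16 groups of 8 to 12 (Setting, The interventions).

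**Method.** Power for two equal groups comes from the noncentral F distribution with 1 and N − 2 degrees of freedom and noncentrality λ = N × (d/2)² = N × 0.0625.

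**Step 1: the plan's own figure.** For N = 128, λ = 8.0 and power is 0.801. The stated 128 for 80% power is reproduced as an unadjusted two-group comparison at d = 0.5.

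**Step 2: the plan's inflation.** 128 × 1.15 = 147.2, rounded up to 148. This reproduces the target. Allowing for a 15% loss by division gives 128 / 0.85 = 150.6, so 151.

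**Step 3: what each enrolment figure leaves at exactly 15% dropout.**

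| Randomised | With data | Unadjusted power |
|---|---|---|
| 128 | 128 × 0.85 = 108.8, about 109 | about 0.73 (0.731 at 108, 0.735 at 109) |
| 148 | 148 × 0.85 = 125.8, about 126 | 0.795 |
| 151 | 151 × 0.85 = 128.4 | 0.80 |

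**Step 4: effect of the planned ANCOVA.** Assume that d = 0.5 is expressed in standard deviations of the post-treatment score and that baseline and outcome correlate at r. Adjustment then acts like raising d to 0.5 / √(1 − r²). The article gives no r, so a range is shown.

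| r (assumed) | Power, 109 with data | Power, 126 with data |
|---|---|---|
| 0 | 0.735 | 0.795 |
| 0.3 | 0.774 | 0.831 |
| 0.5 | 0.848 | 0.895 |

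The correlation at which 109 patients match 128 unadjusted solves 109 / (1 − r²) = 128. This gives r² = 1 − 109/128 = 0.148 and r of about 0.39. The gap between the two enrolment figures is 6.0 points at r = 0, 5.7 at r = 0.3 and 4.7 at r = 0.5.

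**Step 5: do the logistics settle it?** Capacity is 16 × 8 = 128 to 16 × 12 = 192. A total of 128 fills every group to its minimum, and 148 gives 148 / 16 = 9.25 per group. Both fit, so the group plan does not show which figure is meant.

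**The case against.** The best defence is that the Sample size section governs. It is the only section that derives N, the only one that mentions dropout, and it separates the two roles clearly: 128 is enough for the test and 148 is the target. On that reading, the abstract and the Study design section simply repeat the power-analysis figure without the inflation. This is the most natural explanation, and nothing in the article says that recruitment stops at 128. It weakens the practical risk, but two statements about how many patients enter the trial still conflict. Condensing a protocol into an article explains omissions, not two values for one quantity.

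The second defence is that the main analysis is ANCOVA, which the article itself expects to raise power. That stands as a qualification: at a correlation of about 0.39 or more, 109 patients would reach 80%. It does not remove the point, because the article states no correlation and its calculation relies on none.

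Multiple imputation is a weaker defence. It keeps patients without reassessment in the analysis, but in general it does not restore the information lost with their outcomes.

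A reader might also infer more than the article supports:

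- **That the trial has only 73% power.** This requires enrolment to stop at 128, against the stated target, and the comparison to be unadjusted, against the stated main analysis.
- **That nobody could tell whether a final total between 128 and 148 is under-recruitment.** Measured against the Sample size section, such a total is below target. The abstract and design section blur this but do not make it unanswerable.
- **That 148 is itself a material error and more patients are needed.** The dropout rate is given as approximate, and 148 retains 128 at a dropout of 1 − 128/148 = 13.5%. At exactly 15% the power is 79.5%, about half a point below target.

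**Conclusion.** The inconsistency is real: 128 is the number randomised in two places and the number needed before dropout in a third, where the target is 148. It is a minor to moderate consistency correction.

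Its possible size is a fall in power from 80% to about 73%, conditional on three things: enrolment stopping at 128, dropout of 15%, and an unadjusted comparison at d = 0.5 among patients with data. With baseline adjustment and an assumed correlation of 0.3 to 0.5, the same 109 patients give about 77% to 85%. The documents therefore do not establish that the stated power would be missed, only that they give two answers to how many patients will be randomised.

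**What to change.** In the abstract and the Study design section, state that 148 patients will be randomised in order to retain about 128 after dropout, in line with the Sample size section. This is a wording change in two places and adds no patients beyond the existing target.

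If 128 is in fact the number to be randomised, remove the 148 and restate the power under 15% dropout: either about 73% unadjusted, or a figure for the planned ANCOVA with its assumed baseline-outcome correlation stated. The cost is then a different power statement.

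As a minor note, the Sample size section could say that 148 comes from multiplying 128 by 1.15, and that power at exactly 15% dropout is 79.5%. This needs no added patients.

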### Outcome measures

#### Primary outcome

The Yale Brown Obsessive Compulsive Scale (Y-BOCS) is a semi-structured clinical interview which is considered the gold standard for measuring OCD severity [44,45]. The Y-BOCS will be used as primary outcome in the proposed trial.

